### 2.8. Statistical Methods

For the descriptive analysis of the data, normality will be checked with the Kolmogorov–Smirnov and Shapiro–Wilk tests (*n* < 30). Normally distributed variables will be defined by the mean, standard deviation, and value interval, while variables that do not follow a normal distribution will be defined by median and interquartile range. The qualitative variables of the study will be defined by frequencies and percentages.

Regarding quantitative analysis, a correlation analysis (Pearson’s correlation coefficient) will be used to demonstrate the validity of the assessment procedure selected in our study. Cronbach’s alpha coefficient will be used to demonstrate its reliability. For the comparison of two means, Student’s *t*-statistic inferential analysis (parametric test for independent samples), the Mann–Whitney U-statistic (non-parametric tests with two independent samples), and Wilcoxon’s *t*-test (non-parametric tests for repeated means) will be used. The comparison of three or more means has also been used and will be analyzed by means of an ANOVA test in the situation of independent groups (parametric via Snedecor’s F -ANOVA- and non-parametric via Kruskal–Wallis’ H). For repeated measures, Snedecor’s F test will be used in the parametric way and Friedman’s test in the non-parametric way. Correlations will be carried out by two methods: Pearson’s correlation (normal distribution) or Spearman’s correlation (non-normal distribution). Multivariate logistic regression analysis will be performed to determine the variables associated with events of interest. In the logistic regression model, variables that have been significant in the bivariate analysis or that are relevant to the study will be introduced into the logistic regression model. For qualitative or categorical variables, contingency tables and the Chi-Square test of significance will be used when there are two independent samples.

*p*-values of less than 0.05 will be considered significant, i.e., with a confidence interval of 95%. The statistical software IBM SPSS Statistics version 28.0.1 will be used.

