### 2.4. Outcomes

In the initial assessment, all variables, including sociodemographic factors, will be measured. Subsequently, all outcome variables will be assessed at the end of the 8-week intervention.

Personal and sociodemographic variables are as follows:Age (years)Sex (male or female)Weight (kilograms), height (meters) and body mass index (kg/m^2^)Time since diagnosis (years and months)Stage of the disease.Tumor location (colon or rectum).Type of chemotherapy and number of cycles.Radiotherapy (yes/no).

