
### 2.5. Sample Size

The sample size calculation was performed using statistical software (G*Power 3.1). The calculation was carried out for a two-independent-group t-test. The effect size (d = 1.11) was estimated from the mean difference on the Chemotherapy-Induced Peripheral Neuropathy (CIPN) Trial Outcome Index (TOI) scale, obtained from Zimmer et al., 2017 [24], due to the similarity of interventions, and from the study by Balnd et al., 2019 [24], where the same scale (EORTC QLQ-CIPN 20) was used in the same group of patients but with a different intervention. A significance level of 0.05 and power of 95% were established. The estimated sample size was 38 subjects. Taking into account a 20% dropout rate based on the previous study [24], the required number of subjects was 44, with 22 subjects in each group.

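### The arm comparison of CIPN20 rests on unadjusted tests with none named as primary; a pre-specified ANCOVA on baseline CIPN20 would usually be more precise at no extra data cost

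*Protocol article*

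**What the plan says.** **Tests listed (Protocol article, section 2.8).** Two means are to be compared by Student's t, "inferential analysis (parametric test for independent samples), the Mann–Whitney U-statistic (non-parametric tests with two independent samples", and by a Wilcoxon test for repeated measurements. ANOVA or Kruskal–Wallis follows for three or more groups, and an F test or Friedman's test for repeated measures. None of these is tied to CIPN20 or named as the primary analysis, and no model for a continuous outcome has a baseline covariate. Kolmogorov–Smirnov and Shapiro–Wilk checks are introduced under the descriptive analysis. Only the correlations are explicitly made to depend on distribution. The significance rule is that "values of less than 0.05 will be considered significant"; sidedness is not given.

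**Sizing (section 2.5).** "The calculation was carried out for a two-independent-group t-test". "The effect size (d = 1.11) was estimated from the mean difference". "A significance level of 0.05 and power of 95% were established". "The estimated sample size was 38 subjects", raised to 44 for 20% dropout.

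**Baseline data (section 2.4).** "In the initial assessment, all variables, including sociodemographic factors, will be measured". All outcomes are measured again after the intervention.

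**The only multivariable model (section 2.8).** A logistic regression is planned, in which "variables that have been significant in the bivariate analysis or that are relevant to the study will be introduced into the logistic regression model". The event it models is not defined.

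**The concern.** Participants are enrolled while already on chemotherapy (section 2.2), and chemotherapy type and number of cycles are recorded as patient characteristics (section 2.4). Neuropathy at entry may therefore differ between patients, and some of the spread in the final score would be predictable from the baseline score. A two-sample test on final scores leaves that spread in the error term.

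There is also a question of what is estimated. A t-test addresses a difference in means and Mann–Whitney a shift in ranks. With both listed and neither named for CIPN20, the primary estimand is open until the data are seen. In a trial of 44 patients, precision is scarce and the reader needs to know in advance which result counts.

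**Working it through.** **1. Reproducing the stated sample size.** Inputs from section 2.5: d = 1.11, alpha 0.05, power 95%, equal groups. Method: exact noncentral t with noncentrality d·√(n/2) and 2n − 2 degrees of freedom.
- One-sided: 19 per arm, noncentrality 1.11 × √9.5 = 3.42, power 95.6%. Total 38, as stated.
- Two-sided: 19 per arm gives 91.4%; 95% needs 23 per arm, total 46 (power 95.7%).

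So 38 is reproduced only as a one-sided, unadjusted t-test.

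**2. Completers.** 44 × (1 − 0.20) = 35.2, taken as 35 (17 and 18).

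**3. Effect of adjusting for baseline.** The article gives no baseline-to-outcome correlation r, so r is an assumption shown over a range. Adjustment multiplies residual variance by about 1 − r², so the effective standardised difference is d/√(1 − r²). Noncentrality is that value times √(17 × 18/35) = 2.957. It is also assumed that d = 1.11 is in SDs of the final score, which section 2.5 does not say. Two-sided alpha is 0.05.

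| r | 1 − r² | d/√(1 − r²) | Power |
|---|---|---|---|
| unadjusted | 1.00 | 1.110 | 89.0% |
| 0.2 | 0.96 | 1.133 | 90.1% |
| 0.3 | 0.91 | 1.164 | 91.6% |
| 0.4 | 0.84 | 1.211 | 93.5% |
| 0.5 | 0.75 | 1.282 | 95.7% |
| 0.6 | 0.64 | 1.388 | 97.8% |

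The degree of freedom spent on the covariate (32 instead of 33) changes these by no more than about 0.1 point. Power reaches 95% at r of about 0.47.

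**4. A smaller effect.** With d = 0.8 (assumed) and 19 per arm, two-sided power is 67.0% unadjusted, and 71.0%, 79.1% and 91.9% at r = 0.3, 0.5 and 0.7.

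**5. Chance imbalance.** With 22 per arm, the baseline difference between arms has standard error √(2/22) = 0.30 SD. A 0.3 SD imbalance would move the unadjusted difference by r × 0.3, or 0.15 SD at r = 0.5.

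**6. Choosing the test by normality.** Simulation, 6,000 runs per scenario, 19 per arm, r = 0.5, two-sided. The selected test is t if Shapiro–Wilk passes in both arms, otherwise Mann–Whitney.

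| Data | Type I error, selected test | Power at d = 1.11: t | Mann–Whitney | Selected | ANCOVA |
|---|---|---|---|---|---|
| Normal | 4.8% | 91.7% | 89.5% | 91.4% | 96.9% |
| Right-skewed (lognormal type) | 4.7% | about 90% | 97.6% | 97.5% | 93.9% |

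Selection does not inflate type I error here. ANCOVA beats the t-test in both settings, but untransformed ANCOVA is beaten by Mann–Whitney when scores are strongly skewed.

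**The case against.** - **Section 2.8 is a general menu.** It includes a repeated-measures F test, which can use baseline, and it does not say whether the t-test is on final or change scores. A reader might infer that baseline CIPN20 goes wholly unused; the text does not support that. What stands is that the F test is not assigned to the primary outcome or to the arm contrast, and the trial is sized on an unadjusted t-test.
- **Covariates are often left to an analysis plan.** True, but the article does not simply stay silent. It states the two-sample tests and the sizing test, and both are unadjusted.
- **A normality gate is explicit only for correlations.** For the arm comparison it is the most natural reading of the parametric and non-parametric pairs, not a stated rule. The simulation also shows no inflation of type I error, so the cost is an unfixed test and estimand.
- **The unadjusted test is valid.** Its standard error already allows for chance imbalance. A reader might infer bias; under randomisation the loss is precision only.
- **The gain may be small or absent.** At r = 0.2 to 0.3 it is 1 to 3 points, and skewed scores can favour a rank test. This stands, and is why the range is shown and a robust sensitivity analysis is part of the fix.
- **Logistic regression.** Entry is not by significance alone, since relevance also qualifies, and the model is not presented as the treatment comparison. The insomnia scale is described as a screening tool, so a binary event is conceivable. Still, no event is defined among the listed outcomes. Labelling the model exploratory is warranted; requiring its deletion would be preference.

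**Conclusion.** The point holds as an available improvement in precision and clarity, not as an error that invalidates the trial. The article names only unadjusted tests for comparing the arms, fixes none of them for CIPN20, and uses baseline CIPN20 as a covariate nowhere, although it is scheduled to be measured.

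With 35 completers and d = 1.11, ANCOVA would lift two-sided power from 89.0% to between 90.1% (r = 0.2) and 97.8% (r = 0.6). This rests on an assumed r, on d being in final-score SDs, and on roughly normal scores.

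A tempting stronger reading is that the plan has lost power and ANCOVA would restore it. The article does not support that. Its own calculation was for an unadjusted t-test, so omitting ANCOVA loses nothing against it. The shortfall from 95% arises because 38 is reproduced only one-sided and because 44 is too few for 20% dropout (38/0.8 = 47.5, so 48). Those belong to the sample-size section. Adjustment reaches 95% only if r is about 0.47 or more.

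**What to change.** - Name one primary analysis: ANCOVA of end-of-intervention CIPN20 on randomised arm with baseline CIPN20 as covariate, two-sided 0.05, reporting the adjusted mean difference with its 95% confidence interval.
- Use the same model for each continuous secondary outcome with its own baseline.
- Replace any choice of test by normality with a pre-stated rank-based or bootstrap sensitivity analysis, because the scores may be skewed.
- Label the within-arm tests descriptive. Label the logistic regression exploratory, with its event defined, if it is kept.

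The assessment week must be reconciled separately before the model can be finalised: section 2.3 gives a 12-week intervention and section 2.4 an 8-week one.

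The cost is wording in the analysis section, settled before anyone sees outcomes by arm. No extra patients, visits or measurements are needed, since the article already schedules CIPN20 at both time points.

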#### 2.4.1. Primary Outcomes

The primary outcome measures are chemotherapy-induced peripheral neuropathy (CIPN). Self-reported neuropathy was evaluated using the European Organisation for the Research and Treatment of Cancer Quality of Life (EORTC QLQ) CIPN20 questionnaire, comprising 20 items categorized into three subscales that assess sensory, motor, and autonomic symptoms. Each item was rated on a Likert scale from 1 ‘not at all’ to 4 ‘very much’. Scores were then converted to a 0–100 scale, with higher scores indicating greater symptom severity.

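### Section 2.8 enters covariates into a logistic model by bivariate significance, for an undefined event, in 44 patients: about 26–45% of null trials would report a spurious predictor

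*Protocol article*

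**What the plan says.** Section 2.8 states: "Multivariate logistic regression analysis will be performed to determine the variables associated with events of interest". It then gives the entry rule: "variables that have been significant in the bivariate analysis or that are relevant to the study will be introduced into the logistic regression model". The general threshold in the same section is that p-"values of less than 0.05 will be considered significant". The section gives no limit on model size and does not label this analysis exploratory.

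Section 2.4 names no binary endpoint. For the primary outcome, CIPN20, section 2.4.1 says: "Scores were then converted to a 0–100 scale, with higher scores indicating greater symptom severity". The secondary outcomes in section 2.4.2 are also numeric: QLQ-C30 scales (0–100), six-minute walk distance, two HADS scores, FACT-F (0–160), MISS (0–12) and laboratory values. No cut-off is given for any of them.

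Section 2.5 sizes the trial on a difference in means: "The calculation was carried out for a two-independent-group t-test". It randomises 44 patients, 22 per group, and allows for 20% dropout.

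**The concern.** Two choices are fixed in the text, and neither suits this trial.

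First, logistic regression needs a binary outcome, and none of the listed outcomes is binary.

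Second, covariates may enter because they passed a bivariate test in the same data. With few patients and many candidates, such a screen picks up chance associations. The final model then tests the selected variables at 0.05 as though they had been named in advance. The second entry route, relevance to the study, is open-ended and does not limit the model either.

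What is at stake is the credibility of any published statement that a characteristic is associated with neuropathy or another event. The randomised treatment comparison is not at stake.

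**Working it through.** **The plan's own figure.** Section 2.5 gives d = 1.11, alpha 0.05, power 95%, and "The estimated sample size was 38 subjects". A noncentral-t calculation for two independent means gives 19 per arm, 38 in total, with a one-sided test (power 95.6%). A two-sided test needs 23 per arm, 46 in total. So 38 is reproduced with a one-sided test. Sidedness is a separate matter; what counts here is that the plan sizes CIPN20 as a continuous score.

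**Inputs.**
- N = 44 randomised; after 20% dropout, 44 × 0.80 = 35.2, about 35 evaluable (section 2.5).
- Screening and final threshold 0.05 (section 2.8).
- Candidates: section 2.4 lists 8 items, or about 11 single variables if weight, height and BMI are counted separately and so are chemotherapy type and number of cycles. Arm and baseline scores would add more. The range used is 8 to 15 (assumption).
- Event rate 30% to 50% (assumption, since no event is defined).

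**Events per variable.** At a 50% rate the smaller group is 44 × 0.5 = 22; at 30% it is 44 × 0.3 ≈ 13. The guide of 10 events per variable (a rule of thumb, assumed here) allows 22/10 = 2.2, so 2 covariates, or 13/10 = 1.3, so 1. With 35 evaluable patients the smaller group is 17 or 10, allowing 1 covariate. Entering 8 to 10 variables at the best case of 22 leaves 22/8 = 2.8 to 22/10 = 2.2 events per variable.

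**Chance of a false entry.** With k independent unrelated candidates, P(at least one passes) = 1 − 0.95^k.

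**Chance of a spurious final predictor.** Null simulation, 1,500 trials per row: k normal noise covariates, t-test screen at 0.05, then a logistic fit on those that passed.

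| N | k | Event rate | 1 − 0.95^k | Any passes screen | Any significant in final model |
|---|---|---|---|---|---|
| 44 | 8 | 50% | 34% | 32% | 27% |
| 44 | 10 | 50% | 40% | 40% | 32% |
| 44 | 10 | 30% | 40% | 43% | 35% |
| 44 | 11 | 50% | 43% | 43% | 35% |
| 44 | 15 | 50% | 54% | 53% | 42% |
| 35 | 8 | 50% | 34% | 33% | 25% |
| 35 | 10 | 30% | 40% | 39% | 28% |
| 35 | 15 | 50% | 54% | 52% | 39% |

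At proportions near 35%, the simulation standard error is √(0.35 × 0.65/1500) ≈ 1.2 percentage points. Over repeat runs spanning 8 to 15 candidates, the last column ranges from about 26% to 45%. In the simulations tabulated above, 62–76% of the noise variables that passed the screen stayed significant. The mean apparent AUC of the fitted models was 0.71–0.77, where the truth is 0.50.

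**The other entry route.** If 8 to 10 unrelated variables are all entered as relevant, with no screen, 29–45% of null models show at least one significant variable, and the apparent AUC is 0.74–0.84.

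**Only if the event is a split score.** A median split of a normal score keeps about 2/π = 0.64 of the information; 0.64 × 44 ≈ 28 patients' worth. This rests on an assumption that the article does not state.

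**The case against.** The strongest objection is that the article never says CIPN20 or any other score will be dichotomised. It also mentions things that are events in the ordinary sense: serious adverse events (section 3.3), early stopping of treatment for intolerance (section 2.2), and progression or loss of patients (section 3.2). The definition of the event could reasonably sit in an analysis plan that is not shown. This stands. A reader might infer that CIPN20 will be cut at a point chosen after seeing the data, and that the efficacy analysis thereby loses about a third of its information. The documents do not support that. Section 2.5 sizes the trial on a t-test, section 2.8 provides the t-test and Mann–Whitney test for comparing groups, and the logistic model replaces neither.

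It is also fair to say that no objective in the Introduction asks for predictors, that an unadjusted comparison of randomised arms is valid, and that most null trials (55% to 74%, the complement of the range above) would report no false predictor. The candidate count is uncertain too. BMI is computed from weight and height, and tying the three together lowers the 11-variable figures to about 40% passing the screen and 31% significant in the final model. All of this limits the scope and calls for a range.

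None of it rescues the entry rule. That rule is written into the article, so the point does not depend on missing detail, and the relevance route makes the model larger without making it safer.

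**Conclusion.** The point holds as a moderate defect in a side analysis. The stated entry rule is unsuitable at this sample size: the chance of reporting at least one spurious predictor is roughly 26% to 45% when nothing is related to the event, against the 5% that a reader would take from the stated threshold. One or two covariates are supportable at 10 events per variable. These figures assume 8 to 15 independent candidates and event rates of 30% to 50%; correlation among candidates lowers them and further candidates raise them. Spurious findings are a substantial risk, not a certainty.

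The comparison of CIPN20 between arms is not damaged. The 64% information figure is conditional on a median split and should not be read as a property of the plan.

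**What to change.** In section 2.8:

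- Remove entry by bivariate significance.
- For CIPN20, specify a linear model on the 0–100 score with arm, baseline CIPN20 and at most one or two covariates fixed in advance, for example chemotherapy type. Baseline scores are already collected. This is a gain in efficiency; the unadjusted comparison is not wrong.
- If predictors are to be explored, name a short list beforehand, keep scores continuous, and label the results exploratory.
- Keep logistic regression only for a genuinely binary event that is defined in advance, with the number of covariates limited by the expected number of events.

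The cost is a change of wording; no extra data or patients are needed. What is given up is an open-ended predictor search that none of the stated objectives requires.

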## 3. Discussion

### 3.1. Potential Impact and Significance of the Study

Colorectal cancer is one of the leading causes of morbidity and mortality worldwide. Adjuvant treatments, such as chemotherapy and radiotherapy, are essential for reducing the risk of recurrence, but they are often associated with significant side effects that affect patients’ quality of life. Physical exercise has emerged as a promising complementary intervention that can mitigate these adverse effects, improve physical capacity, and enhance the overall well-being of patients. This physical exercise program is specifically designed to address the unique needs of individuals with colorectal cancer undergoing adjuvant therapy, offering an opportunity to improve both clinical outcomes and patients’ quality of life.

Implementing a physical exercise program can reduce cancer-related fatigue, improve mood, and increase energy levels, contributing to a better quality of life during and after treatment. Additionally, regular exercise can help alleviate some of the most common side effects of adjuvant therapy, such as peripheral neuropathy, muscle loss, and general weakness. Previous studies have indicated that exercise can significantly reduce cancer-related fatigue, as evidenced by research from Mustian et al. (2017) [12], where considerable improvement in the quality of life of cancer patients participating in exercise programs was observed.

A structured exercise program can improve patients’ strength, flexibility, and cardiovascular endurance, allowing them to maintain greater independence and functionality in their daily activities. While research such as that by Courneya et al. (2014) [25] has already shown the benefits of exercise in breast cancer patients, this study will focus specifically on colorectal cancer patients undergoing adjuvant therapy, an area that still requires more targeted research. Although more research is needed, preliminary evidence suggests that exercise may positively influence oncological outcomes, potentially enhancing treatment effectiveness and reducing the risk of cancer recurrence. Studies like those by Meyerhardt et al. (2006) [26] have shown that exercise can be associated with lower recurrence rates and higher survival in colorectal cancer patients, reinforcing the need for further exploration in this area.

Participation in an exercise program can also provide patients with a sense of control and empowerment, improving their psychological and emotional state during treatment. This sense of control can be crucial for the emotional well-being of patients, as highlighted in the study by Pinto and Trunzo (2005) [27], where patients engaged in physical activities reported improved self-esteem and psychological well-being. Furthermore, incorporating physical exercise as part of the treatment regimen can promote long-term healthy lifestyle habits, which can have sustained benefits for patients’ overall health. Previous research, such as that by Schmitz et al. (2010) [28], has demonstrated that patients who adopt an active lifestyle during and after treatment have better quality of life and fewer long-term health complications.

In summary, this physical exercise program has the potential to offer significant benefits to individuals with colorectal cancer undergoing adjuvant therapy, improving their quality of life, physical capacity, and possibly their clinical outcomes, while promoting a positive attitude and healthy lifestyle habits. By comparing the expected findings of this study with existing literature, it is evident that this research will significantly contribute to the current knowledge base, providing specific data on the effects of exercise in colorectal cancer patients. This will not only help improve current treatment strategies but also offer valuable guidance for future research and clinical practices in this field.

